#### **IV. Approach.**

##### **A. Overall Design.**

The proposed UH3 study will employ a randomized, parallel-group design to determine the best strategy for mobile testing-and-treatment of PWIDs for HCV. This Type 1 hybrid effectiveness-implementation study will examine the effectiveness of a model of mobile telemedicine service delivery integrated into rural harm reduction programming. The model aims to reach rural opioid injectors who are living with HCV and to fill service gaps identified in our UG3 study around access to syringe services and HCV testing and treatment. Working closely with local harm reduction agencies, we propose to employ a mobile van to expand antibody and viral load testing for HCV, distribute syringes in rural communities with poor access to brick-and-mortar SSPs, and provide HCV telemedicine treatment to rural PWIDs. We will also validate the accuracy of DBS testing for HCV viral load as a potential strategy to address limited access to effective phlebotomy. All consenting PWIDs with HCV antibody present will receive HCV viral load and liver elastography results, and, if current HCV carriers, initial vaccination for HBV and/or HAV. We will then randomize 220 rural PWIDs with current HCV to one of two strategies for HCV work-up and:

(1) Enhanced Usual Care (EUC) -- referral with care navigation to a local or regional treatment provider.

(2) Mobile tele-HCV Care (MTC) -- telemedicine DAA treatment for HCV on a mobile van.

Primary outcomes will be the proportion of PWID who initiate DAA treatment, achieve sustained virologic response at 12-weeks post-treatment (SVR12), and report no syringe sharing in the prior 30 days at follow-up. We hypothesize that, compared with EUC, mobile tele-HCV care will be associated with:

H1: higher rates of DAA treatment initiation,

H2: higher rates of sustained virological response 12-weeks post-treatment (SVR12, a.k.a. cure), and

H3: lower rates of syringe sharing behavior.

Secondary outcomes will examine rates of completing the HBV and HAV vaccination series, starting MOUD, ED visits, as well as health-related quality of life HRQOL and substance use. Qualitative formative evaluation will assess barriers, facilitators, and implementation lessons-learned.

In order to accomplish the research study aims and to be in compliance with Baystate Medical Center (BMC) policies, the DISCERNNE research team will establish a clinical partnership with Better Life Partners (BLP), who will be responsible for all the following clinical activities and tasks:

1. Patient Registration with BLP;
2. Perform clinical activities, including:
  - a. Conduct HCV rapid testing;
  - b. Collect Dried Blood Spot (DBS) sample;
  - c. Phlebotomy (collect and prepare blood samples for lab analysis);
  - d. FibroScan (perform scan, export and send results to study physician).
3. Order, transport, and administer HAV/HBV vaccination.
4. Explain lab results and give referrals for services as appropriate.
5. Assist with ordering HCV medication (for intervention (MTC) group only).
6. Answer clinical/medical questions from participants, as appropriate.

## B. Sampling and Data Collection

The study will seek to enroll PWIDs with untreated chronic HCV infection in the 10 rural study counties adjacent to I-91 and the Connecticut River in NH and VT. The following factors will determine study participation:

### 1. Inclusion Criteria:

- a. Current or past history of drug injection;
- b. Health insurance that will cover HCV medications (study staff will work with those who are eligible but have not signed up for insurance once consented and enrolled in study)
- c. Lives in one of the 10 study counties in NH and VT, and plans to remain in the study region for the next 12 months;
- d. Age 18 years or older;
- e. Speaks English;
- f. Capacity to voluntarily provide informed consent;
- g. Will accept randomized assignment, and participate in follow-up over 12 months;
- h. Will provide releases to access community medical records;
- i. Will provide names and contact information of at least 3 persons for re-contact purposes;
- j. Not previously treated for HCV;
- k. Not pregnant or trying to conceive;
- l. HCV antibody positive on point-of-care rapid test.

### 2. Exclusion Criteria:

- a. Unable to obtain venous blood sample for mandatory laboratory testing
- b. HCV viral load undetectable
- c. Hepatitis B surface antigen (HBsAg) positive;
- d. Significant renal failure (eGFR 30 mL/min/1.73m^2 or less, or end-stage renal disease requiring dialysis);
- e. Decompensated cirrhosis, as manifested by liver fibrosis on elastography (through FibroScan) and/or Fibrosure blood test plus at least one of the following symptoms:
  - i. Jaundice (yellowing of the eyes and skin)
  - ii. Increasing abdominal size (ascites) and leg edema
  - iii. Periods of confusion consistent with encephalopathy
  - iv. History of gastrointestinal bleeding.

### 3. Screening and Eligibility.

The 68% of participants recruited during the UG3 phase who tested positive for HCV antibody will be recontacted for screening. We will also screen PWIDs known to be HCV antibody positive who are referred from community partners or eligible participants until we have randomized 220 PWIDs with current HCV infection. Phone or in-person screening by research staff will determine initial eligibility based on self-report of inclusion criteria.

**Time T0: Screening.** Those who meet these criteria will be invited to the van for *Visit T0*, receive a detailed explanation of the study, undergo informed consent, and receive point of care testing for HCV antibody (if not previously documented) and HIV antibody (**Figure 1**). If an otherwise eligible participant does not have health insurance, the study staff will assist that person with enrolling in health insurance once consented and enrolled in study.

Persons with HCV antibody present will have phlebotomy performed and undergo van-based non-invasive liver transient elastography; those with high scores for cirrhosis or for whom a successful scan (through Fibroscan) is not able to be completed will have the presence of decompensated cirrhosis confirmed by the FibroSure lab test that will be performed on all HCV RNA positive blood samples. Phlebotomy will be attempted no more than three times in one day for each participant. If an individual attempts a confirmatory blood draw, but a blood sample is not able to be drawn (e.g. phlebotomist is unable to access an appropriate vein after no more than three sticks), the participant may return a second day for no more than three attempts.

If a blood sample is not able to be drawn, the participant would still receive the full \$20 payment but would not be eligible to participate if initial lab work cannot be completed. If the confirmatory blood draw is successfully completed, the participant will provide locator information, be paid \$20 for their time and discomfort, and asked to revisit the van to receive their results and the final eligibility determination.

Specimens will be dropped at the Baystate Franklin Medical Center laboratory for courier service to Baystate Reference Laboratories (BRL) for determination of HCV viral load (RNA by PCR). For venous samples that are positive for HCV-RNA, BRL will also test for genotype, hepatitis B surface antigen, antibody, and core antibody (HBsAg, HBsAb, and HBcAb). A serum-separating tube (SST) for creatinine, liver function (ALT, AST and Total Bilirubin) and HCG (where appropriate) will be held by BRL. Specimens obtained from individuals that are positive for HCV viremia will be processed for creatinine, liver function and serum HCG tests (where indicated). We anticipate few post-randomization exclusions on the basis of severe renal failure or pregnancy not previously known. Samples positive for HCV viremia will also be sent by BRL to LabCorp for FibroSure testing to confirm the absence of decompensated cirrhosis and will be prepared for eventual batch shipping to the GHOST lab.

**Visit T1.** Potential participants will return to the van when results have been received.. Study staff will attempt to locate no-show individuals to ensure they receive their laboratory results. Individuals deemed ineligible by laboratory testing will receive a copy of their laboratory results, \$10 for their time, a referral for services as appropriate, and an invitation to receive harm reduction services from the van for the duration of the study. Individuals deemed ineligible due to the presence of decompensated cirrhosis as indicated by the FibroSure test will also undergo a tele-exam with a study physician and be referred to a liver specialist. Eligible participants will perform the baseline ACASI interview (for which they will receive \$20 for their time), receive the initial vaccination for HBV and HAV as indicated, and be randomized to their study assignment. Participants with a positive test for HIV will be referred to an HIV specialist for HIV care, but HCV treatment will still be provided by the study team according to group assignment.

**Randomization (also at Visit T1).** Individuals whose specimens are positive for HCV viremia and negative for HBsAg will be randomly assigned 1:1 to Enhanced Usual Care (EUC) or Mobile Tele-HCV Care. Based on feedback gathered during Community Engagement Studios conducted with UG3 study participants, it was determined that randomization should occur in as transparent a manner as possible to address any potential participant concerns around bias or personal discrimination. During Visit T1, eligible participants will sit down with research staff and will witness the randomization process, which will be done using a computer program that utilizes block randomization in real time. Computerized block randomization will ensure balance by study site, gender, and current (last 30 days) drug injection.

[figure not shown]

**Figure 1. Recruitment and Study flow.** Staff on the van will also offer Narcan nasal inhalers, cottons, sterile water, clean cookers, rubber tourniquets, condoms and sterile syringes (provided by harm reduction partners purchased from non-federal sources) at every visit. If resources permit, services would be provided to anyone who approaches the van, but at a minimum, to all who have initiated study procedures (eligible and ineligible).

## 4. Study Conditions

**a. Group 1: Enhanced Usual Care (EUC).** At **Visit T1**, eligible participants assigned to EUC will meet the care navigator who will arrange referral for HCV treatment with local or regional clinicians, and receive a copy of their test results and information about the initial dose of vaccine they received to bring to the clinician. The care navigation, vaccination, and provision of test results represent significant enhancements to usual care, and may help reduce the high no-show rate for clinical referrals in this population.

**Care Navigation.** All EUC participants will receive care navigation for HCV treatment. Care navigation will be adapted from existing medical case management services for HIV in consultation with our harm reduction partners. Care navigation will be provided by staff from harm reduction partners and by study staff. Navigation will be tailored to the participant and trauma-informed. The complete manual for HCV care navigation will be

developed in collaboration with harm reduction partners and community stakeholders (including referencing and adapting some of the resources they use for SSP management) in the first quarter of the project.

Care navigation will focus on HCV care coordination and will include maintaining health insurance enrollment, coordination of study visits, provision of harm reduction services, and establishment of a care coordination agreement so the care navigator and study team can communicate with providers and other members of the care team. The Care Navigator will also perform an initial assessment of other needs to address social determinants of health and connect participants to available resources, primarily via referrals to harm reduction partners (e.g. MOUD, primary care, visits to the ED, housing, transportation, employment, etc.). EUC participants will have care navigation services for the duration of HCV treatment or, for those who do not initiate treatment, to a maximum duration of 16 weeks.

**b. Group 2: Mobile Tele-HCV Care (MTC).** At *Visit T1*, eligible participants assigned to MTC will receive telemedicine visits via Zoom or a similar platform with a medical clinician with the help of the medical assistant or other study staff. Both VT and NH Medicaid cover telemedicine visits without an initial in-person visit. Where possible, DAA treatment will be started at this visit or mailed to the client. The medical assistant or study staff will facilitate consent for treatment, and registration of the patient for the visit with the clinician's institution. An appropriate clinical bill will go to insurance; this process will facilitate sustainability. Follow-up clinical telemedicine visits will be at the discretion of the clinician, with participant meeting the medical assistant for a check-in visit (with study clinician on call, as needed) at week 4 after treatment initiation to monitor initial response and safety, and at end-of-treatment (8 or 12 weeks depending on DAA regimen). Follow-up HBV and HAV vaccines will be scheduled to be given on the van as indicated.

*Tele-treatment of HCV with DAAs.* Participants in the MTC group will be offered treatment with DAA. In the absence of contra-indications, the pan-genotypic regimen containing glecaprevir-pibrentasvir (Mavyret) will be preferred; the treatment duration is 8 weeks in the absence of cirrhosis, or 12 weeks in the presence of cirrhosis. Patients with mild to moderate renal insufficiency will be offered pan-genotypic sofosbuvir-velpatasvir (Epclusa) for 12 weeks, regardless of the presence of cirrhosis.

## 5. Data Collection

**a. Audio Computer Assisted Survey Instrument (ACASI).** Drs. [name] and [name] led development of a harmonized quantitative survey with partners in all eight Rural Opioid Initiative (UG3) sites in 2017-2018. Of the eight UG3 sites, five are currently using the ACASI version developed at the Tufts University School of Medicine. The other three sites are using the harmonized survey in CAPI platforms (RedCap, Qualtrics). Survey domains that are included in all harmonized instruments include: sociodemographics; substance use; injection behavior (including syringe sharing), sex risk behavior, overdose prevalence, substance use treatment, and sexual-mediated risk behaviors; self-reported infectious disease and health status; access to harm reduction (e.g., SSPs, naloxone), MOUD, and health care services; knowledge, attitudes, and experience with such services; geospatial locations of community assets, risks, and place of residence; mobile phone and texting practices and experiences; criminal justice involvement and egocentric and sociometric social networks.

As in the UG3 phase, we will develop and deploy a modified version of our existing ACASI harmonized across the ROI sites to assess participants at baseline and follow-up. We will incorporate domains focused on HCV screening, confirmatory testing, and treatment experiences; telehealth exposure, experience, and satisfaction; additional measures focused on enhanced syringe access, syringe sharing and injection-mediated risks; and experience and satisfaction with our mobile harm reduction and tele-care van. Final core survey questions will be harmonized with those decided upon by the UH3 National Executive Steering Committee. Drs. [name] and [name] are ready and willing to assist the Data Coordinating Center (DCC) with harmonization of measures and instruments across all funded UH3 sites. Where applicable, we will use common data elements such as those from the National Library of Medicine.

**b. Follow-up Interval.** All participants will have one brief check-in visit approximately 4 weeks after treatment initiation to order more medication or consult with physician (via telemedicine or over the phone, as

needed) if necessary for MTC group, and to check on status of local provider HCV treatment for EUC group. There will then be four follow-up visits: at end-of-treatment (week 8 or 12 after treatment initiation), then approximately 12, 24, and 36 weeks after end-of-treatment to monitor for reinfection. Respondents will complete the ACASI at each follow-up. These assessments will include an HCV-RNA viral load at each follow-up. Once the DBS testing is validated (see below) follow-up viral load testing will no longer utilize venipuncture to determine reinfection. Individuals who do not initiate HCV treatment will have follow-up visits timed as if they had started 8-weeks of treatment 8 weeks after T1. In other words, for those who do not initiate treatment, follow-up will occur approximately 16, 28, 40, and 52 weeks after the T1 visit.

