1. Perform a Type 1 hybrid effectiveness-implementation study to examine the effectiveness of a model of mobile telemedicine treatment for HCV integrated with syringe services programming, versus the current clinical practice of referral to a local or regional provider, enhanced with care navigation.
2. Validate the accuracy of dried blood spot (DBS) testing for HCV viral load as a potential surveillance strategy to address limited access to phlebotomy services in rural areas.

Working closely with harm reduction experts in rural communities with poor access to sterile syringes, we will employ a mobile syringe services van to expand HCV antibody and viral testing, bolster syringe access, and provide HCV telemedicine treatment. PWIDs who tested positive for HCV antibody during the UG3 phase will be re-contacted, with supplemental sampling from local referrals. All consenting PWIDs with HCV antibody present will undergo DBS fingerstick and venipuncture for HCV viremia, and, as appropriate, receive initial hepatitis B virus (HBV) and/or hepatitis A virus (HAV) vaccines. We will then randomize them (n= 220) to one of two strategies for HCV work-up and treatment among rural HCV-infected PWIDs:

- (1) Enhanced Usual Care (EUC) – referral with care navigation to a local or regional HCV treatment provider.
- (2) Mobile tele-HCV Care (MTC) – HCV telemedicine Direct-Acting Antiviral treatment for HCV (DAA) on a mobile van.

Primary outcomes will be the proportion of PWID who initiate DAA treatment, achieve sustained virologic response at 12-weeks post-treatment (SVR12), and report no syringe sharing in the prior 30 days at 12-week follow-up. We hypothesize that, compared with EUC, mobile tele-HCV care will be associated with higher rates of DAA treatment initiation, higher rates of sustained virologic response 12-weeks post treatment (SVR12, a.k.a. cure), and lower rates of syringe sharing behavior. Secondary outcomes will examine HAV and HBV vaccination completion rates, medication for opioid use disorder (MOUD) initiation, ED visits, health-related quality of life (HRQOL) and substance use. Formative evaluation will assess barriers, facilitators, and implementation lessons-learned.

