#### **5. Plans for interim analysis.**

At least quarterly during one of its weekly meetings, the Executive Committee will review AE and SAE reports for safety issues, recruitment attainment (including participants screened, impact of eligibility criteria, refusal, and expected accrual rate), balance of key characteristics on randomization, follow-up adequacy (including follow-up rates and on-time rates (within 2 weeks), and missing data on key variables (including HCV viral load). This information will be compiled and shared with the DSMB at its periodic meetings. One formal interim analysis for efficacy is planned for when half of enrolled participants have been evaluated for sustained virologic response at 12-weeks post-treatment (SVR12).

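### Syringe sharing is read at a time since randomisation that differs by arm, and the interim trigger favours fast starters; how much either matters depends on delays the protocol does not state

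*Protocol*

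**What the plan says.** Randomisation takes place at Visit T1, where participants "will be randomly assigned 1:1 to Enhanced Usual Care (EUC) or Mobile Tele-HCV Care" (Protocol IV.B.3). Follow-up then runs on two clocks (IV.B.5, Follow-up Interval; repeated under Data and Safety Monitoring, D.1):

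- Initiators are seen "at end-of-treatment (week 8 or 12 after treatment initiation), then approximately 12, 24, and 36 weeks after end-of-treatment".
- Non-initiators are "timed as if they had started 8-weeks of treatment 8 weeks after T1", which the protocol spells out: "for those who do not initiate treatment, follow-up will occur approximately 16, 28, 40, and 52 weeks after the T1 visit".

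The survey that records syringe sharing follows the same clocks: "Respondents will complete the ACASI at each follow-up". Specific Aims defines the sharing outcome as the proportion who "report no syringe sharing in the prior 30 days at 12-week follow-up".

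The arms are expected to start treatment at different times. For MTC, "Where possible, DAA treatment will be started at this visit or mailed to the client" (IV.B.4). EUC participants start after referral to an outside clinician, with no stated delay. The one formal efficacy look comes "when half of enrolled participants have been evaluated for sustained virologic response at 12-weeks post-treatment (SVR12") (Data and Safety Monitoring, E.5). Section E.6 sets its boundary at p = 0.003, and crossing it stops enrolment.

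**The concern.** Whether and when a participant starts treatment are both consequences of assignment. A visit clock tied to treatment start therefore places the sharing assessment at a different time since randomisation in each arm, and makes the timing of one primary outcome depend on another (treatment initiation). If sharing changes over the months after enrolment, part of any difference between arms would reflect calendar position and not the intervention.

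The same clock decides who is in the interim data. A trigger based on the first half to be evaluated admits people who started quickly before people who started slowly. If start times differ by arm, the interim set is not a balanced sample of those randomised. The efficacy boundary, and the conditional power under observed data used for futility, are then computed on a selected subset.

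**Working it through.** **The plan's own figures.** The non-initiator schedule reproduces: notional start at week 8 plus an 8-week course gives 16; adding 12, 24 and 36 gives 28, 40 and 52. The stated power for sharing also reproduces: 66% vs 47% with 110 per arm, two-sided 5%, gives 81.6%, and 77% vs 58% gives 85.8%, against a stated minimum of 80%. Neither is in question.

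**Timing of the sharing assessment.** For an initiator, week after T1 = start delay + course length + 12. For a non-initiator it is 28.

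| Participant | Week after T1 |
|---|---|
| MTC, starts at T1, 8-week course | 0 + 8 + 12 = 20 |
| MTC, starts at T1, 12-week course | 0 + 12 + 12 = 24 |
| Non-initiator, either arm | 28 |
| EUC, starts at week 4, 8, 12 or 16, 8-week course | 24, 28, 32 or 36 |

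Arm means use the planned initiation rates (70% and 50%, IV.E Sample size), 8-week courses, and assumed mean start delays of 2 weeks (MTC) and 10 weeks (EUC):

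- MTC: 0.7 × (2 + 20) + 0.3 × 28 = 15.4 + 8.4 = 23.8 weeks
- EUC: 0.5 × (10 + 20) + 0.5 × 28 = 15 + 14 = 29.0 weeks
- Gap: 5.2 weeks

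With EUC starting at week 4 to 16, the gap is 3.6 to 9.6 weeks if MTC starts at T1, and 0.8 to 6.8 weeks if MTC starts at week 4. Initiation rates alone produce a gap: with a common delay L in both arms it is 0.2 × (28 − (L + 20)) = 0.2 × (8 − L), which is 1.6 weeks at L = 0 and zero only at L = 8.

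The gap does not depend on which follow-up visit is used. An MTC participant starting an 8-week course at T1 is seen at weeks 8, 20, 32 and 44, and a non-initiator at 16, 28, 40 and 52: 8 weeks apart every time.

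**Interim set under no true effect.** The protocol gives neither the accrual period nor the EUC delay, so these are assumptions: 220 participants accrued uniformly, 60% initiation and 65% cure among initiators in both arms (true SVR12 0.60 × 0.65 = 39%), MTC delay 0 to 4 weeks, 8-week courses, no dropout, non-initiators counted at week 28, and a look at the 110th evaluation; 4,000 simulated trials. The nominal chance of crossing in MTC's favour is half of 0.003, or 0.15%.

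With EUC delays of 4 to 16 weeks:

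| Accrual (weeks) | Interim SVR12, EUC / MTC | False MTC lead | Crossing for MTC |
|---|---|---|---|
| 26 | 36.1% / 45.0% | 8.9 points | 1.65% |
| 52 | 37.5% / 42.3% | 4.8 points | 0.73% |
| 78 | 38.3% / 41.4% | 3.1 points | 0.38% |

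A repeat over 26 to 104 weeks of accrual gives 2 to 9 points and 0.2% to 1.9%. With EUC delays of 0 to 8 weeks it gives 0.7 to 2 points and 0.13% to 0.3%. The Monte Carlo standard error at the nominal rate is √(0.0015 × 0.9985 / 4,000) ≈ 0.06 percentage points, so those crossing rates are close to nominal.

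A variant with 50% initiation and 35% SVR12 in both arms gives leads of 0.7 to 2.1 points (0 to 8 weeks) and 2.8 to 10.0 points (4 to 16 weeks).

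Taking the first 110 randomised instead gives about 39% in each arm and about 0.2% crossing.

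**The case against.** **A reader might infer that the sharing result is biased towards MTC.** The protocol does not support this. The gap is known only in weeks, on a 30-day recall item, and no time trend in sharing is given. Van harm-reduction supplies are offered to both arms. If sharing falls with longer access to them, the later-assessed EUC arm would look better, which works against the hypothesis. The week-8 notional start is also a deliberate partial alignment: it places non-initiators with people who start an 8-week course at week 8. What stands is that nothing aligns the arms, so the comparison is not made at one time since randomisation.

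**The sharing time point is loosely fixed.** Only Specific Aims attaches 12 weeks to it; IV.A and IV.E speak of follow-up without a week, and the choice of model can be left to a statistical analysis plan. This is fair, but every visit carries the same offset, so any comparison by visit number inherits it.

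**A reader might infer that the interim error rate is badly inflated in any case.** It is not. If EUC starts within 8 weeks, the boundary behaves almost as stated. In the 52-week-accrual simulation at the planned rates, EUC initiators are then slightly over-represented too (54% against a true 50%), because anyone starting before week 8 is evaluated ahead of non-initiators. Crossing of up to 7% requires EUC delays of 4 to 24 weeks together with 26-week accrual, and neither figure is in the protocol. With 26-week accrual all 220 are already enrolled at the look, and with 52-week accrual 97% to 100% are, so stopping enrolment would change little. A premature efficacy claim would remain possible.

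**The DSMB approves the interim analysis plan.** It may define the set there, but the trigger written in E.5 is by evaluation and not by randomised cohort.

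**Conclusion.** The concern holds in a limited form. That the sharing assessment falls at different times since randomisation follows from the protocol's own schedule: week 20 for an MTC participant starting an 8-week course at T1, week 28 for a non-initiator, and delay plus 20 weeks for an EUC initiator on 8 weeks. The mean gap of about 5 weeks rests on assumed delays, and its effect on sharing cannot be sized or signed from the document.

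The interim trigger over-represents fast starters. The false MTC lead is about 1 to 2 points with error near nominal if EUC starts within 8 weeks. It is about 2 to 9 points, with 0.2% to 2% crossing instead of 0.15%, if EUC starts at 4 to 16 weeks and accrual runs 26 to 104 weeks. The skew concerns the interim look only: at the final analysis all randomised participants can be counted for SVR12. The timing gap for sharing remains at the end.

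**What to change.** 1. **Sharing.** Define the outcome at a common time since randomisation and estimate it from the existing surveys, for example with a repeated-measures logistic model in weeks since T1, contrasted at about week 28. That week lies between scheduled visits for an MTC participant starting an 8-week course at T1 (20 and 32) and on a scheduled visit for non-initiators. Keep the treatment clock for the SVR12 blood draw only.
2. **Interim set.** Define it as the first 110 randomised, analysed when all have passed one pre-stated time since T1. State one rule for counting those without a documented SVR12 by then. The fixed time is needed because the protocol sets no latest treatment start, so waiting for every case to resolve would have no end.

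The cost is revised wording and a somewhat later interim look. There are no extra visits, no change in sample size and no change to treatment schedules.
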